# Robotic versus open ventral hernia repair (ROVHR): a randomized controlled trial protocol

**DOI:** 10.1007/s10029-025-03299-7

**Published:** 2025-03-04

**Keywords:** Ventral hernia, Retromuscular repair, Robotic ventral hernia, Open ventral hernia

## Abstract

**Background:**

Robotic retromuscular hernia repair has proven to be feasible and safe but lacks randomized data to demonstrate significant clinical benefit. The majority of current comparative studies published have been case series, retrospective studies, systematic reviews, or large registry data, all of which have significant limitations and bias (Bittner et al. in Surg Endosc 32:727–734. 10.1007/s00464-017-5729-0, 2018; Bracale et al in Hernia 25:1471–1480. 10.1007/s10029-021-02487-5, 2021; Carbonell in Ann Surg 267:210–217. 10.1097/SLA.0000000000002244, 2018; (Warren et al. in Surg Endosc. 10.1007/s00464-024-11202-1, 2024; Dewulf et al in BJS Open 6:zrac057. 10.1093/bjsopen/zrac057, 2022; Maskal and Beffa in Surg Clin N Am 103:977–991. 10.1016/j.suc.2023.04.007, 2023). It was only recently that the first randomized trial was conducted by Warren et al. comparing open and robotic retromuscular hernia repairs with synthetic mesh (Warren et al. in Surg Endosc. 10.1007/s00464-024-11202-1, 2024). The data currently available has yielded inconsistent outcomes leaving significant knowledge gaps for clinical decision making. Reduced length of stay for robotic retromuscular repairs has been a consistently proven outcome, however, and therefore, we hypothesized that robotic retromuscular hernia repairs would be superior to open retromuscular hernia repair by reducing length of stay in the hospital by 24 h (Carbonell in Ann Surg 267:210–217. 10.1097/SLA.0000000000002244, 2018).

**Methods:**

The Institutional Review Board at all participating sites has approved this protocol. This trial has been registered on clinicaltrials.gov (NCT: 05472987). The ROVHR trial is a registry-based, multicenter, double-blinded randomized trial. The primary hypothesis is robotic retromuscular hernia repairs is superior to open retromuscular hernia repairs by reducing length of stay by at least 24 h. Secondary outcomes include 30-day wound morbidity, readmissions, opioids prescribed and consumed, NRS-11 pain scores obtained daily for the 5 first days after surgery, PROMIS-3a Pain Intensity survey, and patient reported outcomes including Hernia-Related Quality of Life (HerQLes), and EuraHS. Additionally, direct operating room costs will be compared.

**Discussion:**

Based existing literature, we designed a randomized trial with a primary endpoint to determine if robotic retromuscular hernia repairs reduce length of in hospital stay by at least 24 h compared to open retromuscular hernia repairs. This study will add high-level of evidence providing evidence-based outcomes for clinical decision making.

**Trial registration:**

NCT05472987. Registered on July 20, 2022.

## Introduction

### Background and rationale

Open surgery to correct fascial defects in the abdominal wall has long been considered the gold standard for abdominal wall reconstruction and complex hernia repair, including component separation techniques [7]. Retromuscular hernia repairs for these complex hernias has been favored and endorsed by societal [8, 9]. As surgical innovation and technology advanced, the robotic platform enable surgeons to perform the same a minimally invasive approach to abdominal wall reconstruction. Essentially converting a surgery that traditionally required an open incision to a minimally invasive one [6].

The selection of hernia repair technique is complex and individualized. The techniques available to the hernia surgeons are vast and include open, endoscopic, laparoscopic, hybrid, and robotic techniques, each with their own set of risks and benefits. The data driving surgeon decision based on approach is low quality leaving the surgeon to choose the type of repair based on the hernia morphology, patient co-morbidities, hospital resources, and surgeon training. The need to compare these various surgical techniques remains an ongoing investigative effort with aims to identify where the benefit lies for each individual technique to the patient. With the growth of robotic hernia surgery in the United States, these techniques require evaluation [6, 10].

Therefore, we designed a randomized trial based on previously published retrospective and prospective data that consistently favor robotic retromuscular repair when compared to open retromuscular repairs by reducing in-hospital length of stay.

### Explanation for the choice of comparators

The control arm will be open ventral retromuscular hernia repairs with synthetic mesh. The intervention arm will be robotic retromuscular ventral hernia repair with synthetic mesh.

## Objectives

**Primary Outcome:** To determine if robotic retromuscular ventral hernia repair can reduce in hospital length of stay (LOS) by at least 24 h compared to open retromuscular ventral hernia repair.

**Secondary Outcomes:** Baseline, 30-day, and one-year clinical outcomes include: surgical site occurrence (SSO); surgical site infection (SSI) (superficial or deep); surgical site occurrence requiring procedure (SSOPI); reoperation; mesh excision and other peri-operative complications (ileus, VTE, UTI, etc.). Additionally, readmissions, opioids prescribed and consumed and NRS-11 pain scores obtained daily while standing for the first 5 days after surgery will be recorded. Baseline, 30-day, and one year patient reported outcomes include PROMIS 3a SF, Hernia-related Quality of Life (HerQLes), and EuraHS. Direct costs and operating time will be recorded and compared between the two arms.

After one year, hernia recurrence will be reported via hernia recurrence inventory with or without physical exam or CT-scans following a pragmatic composite recurrence definition.

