### Sample size

Using an alpha of 0.05, a power of 0.90, and determining a 24-h difference in length of stay, the necessary sample size is 86 patients in each arm, yielding a total of 172 patients. Estimating 10% attrition at 30 days, 200 patients would be needed, 100 patients enrolled in each arm.

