### Statistical methods

#### Statistical methods for primary and secondary outcomes

All analyses will be conducted on intention to treat basis (ITT). An ACHQC statistician will perform analyses from all participating centers and will require access to identifiable data. A DUA will be executed prior to sharing of PHI. Patient characteristics and operative comparisons will be summarized by the treatment group. Any departures from ITT will be documented and reported.

Participants’ clinical and demographic characteristics will be summarized by treatment arms. Differences between two groups will be assessed using Wilcoxon rank sum tests for continuous variables and Chi-square or Fisher’s exact tests for dichotomous variables. One-sided p-values less than or equal to 0.05 will be considered statistically significant.

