### Primary analysis

The primary outcome for this study is length of stay measured in hours. Length of stay will start at the time of surgery start and will end when discharge order is placed. Analysis will be performed using the intent to treat analysis. The comparison in length of stay between two groups will be conducted by using two-sided Wilcoxon ranked sum test with significance level of 0.05. Two sample student’s t-test with log-transfomation would also be considered if we are interested to interpret the length of stay with mean and standard error. Per-protocol analysis will also be done if there’s excessive non-adherence or switching groups during the study. Tipping point analysis will be performed when loss of follow up is anticipated.

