## Discussion

Robotic retromuscular hernia repairs have been shown to be safe, effective, and potentially beneficial to patients compared to open techniques [3, 5, 6, 8, 17, 18], but still lacking high quality data. Recently, a randomized trial comparing robotic to open abdominal wall reconstruction for ventral hernias was published [4]. There are some important limitations to this trial including the primary outcome being composite wound morbidity in early post-operative period [1]. These cohort of patients have a planned long term follow up which will be interesting to see if any benefit exists to having a minimally invasive approach to abdominal wall reconstruction. This addition of a randomized trial adds significant value to the current body of literature in the field.

Other retrospective data currently exists. A large case control study found no difference in intraoperative complications between robotic and open TAR (8.9% vs 16.5%, *P* = 0.137) and an 8.9% conversion rate to open. Yet other retrospective series highlights lower estimated blood loss, but without difference in transfusion requirements [6]. Carbonell and colleagues published a 2:1 propensity score matched cohort study of robotic and open retromuscular ventral hernia repairs from the ACHQC in 2018 [3]. This data demonstrated a significantly higher SSO incidence in the robotic group, which was driven by a higher rate of seromas not requiring intervention. There was noted to be a decreased hospital length of stay. This benefit seems to be a recurring consistent advantage of the robotic approach when compared to open retromuscular ventral hernia repairs in retrospective studies [1, 3, 5, 6]. The remaining studies published have been case series, systematic reviews, or large registry data, all of which have significant limitations and inherent bias due to trial design [2].

Based on the available literature, we designed a randomized, double-blinded trial comparing robotic to open ventral hernia repairs using retromuscular techniques. We hypothesized that robotic retromuscular repairs will be superior to open by reducing length of stay by at least 24 h compared to open repairs. This will provide high-quality data to help surgeons make important clinical decisions regarding the care they provide for patients.

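### The primary objective claims a length-of-stay reduction of at least 24 h, but the primary test can show only that stay differs between arms

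*Protocol article*

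**What the plan says.** The 24 h threshold is written as the thing to be shown. The Objectives section of the protocol article gives the primary outcome as "To determine if robotic retromuscular ventral hernia repair can reduce in hospital length of stay (LOS) by at least 24 h" compared with open repair. The Methods paragraph of the abstract labels it the primary hypothesis: "The primary hypothesis is robotic retromuscular hernia repairs is superior to open retromuscular hernia repairs by reducing length of stay by at least 24 h". The Discussion paragraph of the abstract describes the primary endpoint in the same terms, and the main Discussion repeats that robotic repair will be "superior to open by reducing length of stay by at least 24 h compared to open repairs".

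The analysis sections contain no such threshold. Under Primary analysis: "The comparison in length of stay between two groups will be conducted by using two-sided Wilcoxon ranked sum test with significance level of 0.05". The section on non-adherence and missing data repeats this sentence. As an optional addition, a "t-test with log-transfomation would also be considered if we are interested to interpret the length of stay with mean and standard error". Sample size uses 24 h as an input to the power calculation: "Using an alpha of 0.05, a power of 0.90, and determining a 24-h difference in length of stay", which gives 86 per arm, raised to 100 per arm for 10% attrition.

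**The concern.** A rank-sum test has equality of the two distributions as its null hypothesis. Rejecting it says nothing about whether the reduction exceeds 24 h, because 24 h does not enter the test. The optional t-test on log length of stay does not help, since its null is a ratio of 1 rather than a difference in hours. Sizing a trial to detect 24 h does not turn 24 h into a tested threshold: a trial with high power at 24 h will also reject for observed differences well below it.

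At stake is the headline conclusion. If the hypothesis is a reduction of at least 24 h and the only criterion is p < 0.05, a significant result of 14 or 15 h meets the criterion without supporting the hypothesis. The Discussion says the trial is meant to inform surgeons' decisions, so the claim and the evidence for it should match.

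**Working it through.** **Inputs from the protocol article.** Planning difference 24 h, alpha 0.05, power 0.90, 86 per arm evaluable and 100 per arm enrolled (Sample size); two-sided test (Primary analysis); 1:1 allocation (Sequence generation). No SD is given, so 86 per arm cannot be reproduced directly. The calculations take the stated power as correct and use a normal approximation to a difference in means.

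**Implied standard error.** Power of 0.90 at two-sided 0.05 requires 24 / SE = 1.960 + 1.282 = 3.242. With 86 per arm, SE = 24 / 3.242 = 7.40 h. With 100 per arm, SE = 7.40 × √(86/100) = 6.87 h.

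**Smallest significant observed reduction.**
- 86 per arm: 1.960 × 7.40 = 14.5 h. Equivalently, (1.960 / 3.242) × 24 h, about 0.60 of the planning difference. The SD cancels.
- 100 per arm: 1.960 × 6.87 = 13.5 h.

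**Implied SD (an assumption, not a figure in the document).** SD = SE / √(2/n) = 7.40 / √(2/86) = 48.6 h. Allowing for Wilcoxon efficiency relative to the t-test, 48.6 × √0.955 = 47.4 h and 48.6 × √0.864 = 45.1 h. If alpha is read as one-sided 0.05, 24 / (1.645 + 1.282) = 8.20 h and SD = 8.20 / √(2/86) = 53.8 h. The range is about 45 to 54 h.

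**Chance of significance when the true reduction is below 24 h**, as Φ(true / SE − 1.960) with 86 per arm and SD 48.6 h:

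| True reduction | Calculation | Probability |
|---|---|---|
| 12 h | Φ(1.62 − 1.96) | about 37% |
| 18 h | Φ(2.43 − 1.96) | about 68% |
| 24 h | Φ(3.24 − 1.96) | 90% (the design value) |

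**What the data would have to show for the stated claim.** An observed reduction of exactly 24 h has a 95% confidence interval of 24 ± 14.5, or about 9.5 to 38.5 h. With 86 per arm, the lower limit reaches 24 h only if the observed reduction is about 24 + 14.5 = 38.5 h.

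**Sensitivity to sidedness.** The general methods text says "One-sided p-values less than or equal to 0.05 will be considered statistically significant", which conflicts with the two-sided primary test. That is a separate point. On the one-sided reading the threshold with 86 per arm is 1.645 × 8.20 = 13.5 h, and the conclusion is the same.

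**The case against.** The strongest reply is that 24 h is simply the planning difference, loosely worded. There is support for this. Sample size treats it that way, the Background paragraph of the abstract speaks of a 24 h reduction without the at-least qualifier, the Outcomes section lists length of stay in hours with no threshold, and no section mentions a margin or a null other than no difference. Test and sample size agree with each other as a conventional superiority design. This reading is probably what was intended, but it does not fit the Objectives, two paragraphs of the abstract and the main Discussion. If it is the intended meaning, those places need correcting.

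It is also fair that no section says p < 0.05 will be reported as proof of a 24 h reduction. That risk is inferred from the wording of the hypothesis.

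Three stronger readings are tempting and are not supported:
- A reader might infer that the trial is badly underpowered, because the chance of a lower limit above 24 h is only 2.5% when the true reduction is exactly 24 h. That figure is the one-sided alpha at the boundary of any null hypothesis and would be the same in a trial of any size. It also refers to a margin test that nobody planned.
- A reader might infer that the plan lacks an effect estimate with a confidence interval. The article is condensed and an analysis plan may exist, so that absence is not a finding. The article does contemplate reporting a mean with its standard error.
- A reader might infer that the Wilcoxon test is wrong. It is a valid test of whether stay differs between arms.

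**Conclusion.** The point holds as a contradiction between the stated objective and the fixed primary test. Even a clearly significant result would support shorter stay, not stay shorter by at least 24 h. An observed reduction of about 0.60 of the claimed threshold is enough for significance: about 14.5 h with 86 per arm or 13.5 h with 100.

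These thresholds do not depend on the unstated SD, provided the stated 90% power is correct. They are mean-difference equivalents: the planned test works on ranks, and length of stay is probably skewed, so they indicate scale and are not exact cut-offs. The 37% and 68% figures also carry the back-solved SD as an assumption. The validity of the primary test, its type I error and the sample size are unaffected. What changes is the conclusion a positive result may carry.

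**What to change.** Restate the primary objective and hypothesis, in the Objectives, the abstract and the Discussion, as superiority: the null is no difference in length of stay, and 24 h is named as the planning difference. Keep the Wilcoxon test and the sample size.

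Report the difference in hours with a 95% confidence interval. The Hodges-Lehmann shift pairs naturally with the rank-sum test but assumes a location shift, which sits uneasily with the log-scale alternative; a difference in means or medians would also serve. Name one in advance.

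Add one rule: a reduction of at least 24 h is claimed only if the lower confidence limit for the reduction is 24 h or more. Otherwise report that robotic repair shortens stay, if the test shows it, with the interval.

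This costs wording and one estimate, with no extra patients or data. The permitted claim becomes more modest, since the 24 h claim would need an observed reduction of roughly 38.5 h with 86 per arm. It is also a late amendment: Trial status has recruitment starting in July 2022 and expected to finish in July 2025. It should be made and dated before outcome data are analysed.

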### Trial design

This is a multi-center, registry-embedded, double-blinded, randomized controlled trial. Study data will be captured in the Abdominal Core Health Quality Collaborative (ACHQC) registry and supplemented with Research Electronic Data Capture (REDCap®) for variables outside of the ACHQC. These include LOS measured in hours, operating time, direct cost, NRS 11 pain scores, and EuraHS scores.

## Methods: Participants, interventions and outcomes

### Study setting

Cleveland Clinic is the primary site, with additional participating sites including University of Tennessee, University of Florida, and Prisma Health.

### Eligibility criteria

*Inclusion criteria*:Adults ≥ 18 years old.Midline ventral hernia defects ranging from 7 to 15 cm in greatest width as measured by pre-operative CT scan without Valsalva maneuver.Non-emergent caseBody mass index (BMI) less than or equal to 45Patient deemed either a robotic or an open candidate by the operating surgeon

*Exclusion criteria*:Patients 17 years old or youngerPrisonersEmergent casesBMI greater than 45Hernia defects less than 7 cm or greater than 15 cm in width as measured by pre-operative CT scan without Valsalva

### Interventions

#### Intervention description

Patients will be enrolled in an elective setting who are planning to undergo ventral hernia repair surgery at Cleveland Clinic main campus or the other participating sites. After appropriate documentation of inclusion and exclusion criteria, informed consent will be obtained.

**Open retromuscular mesh hernia repair (Control arm):** during open surgery the previous midline scar, if present, is excised, however, if not present than a midline laparotomy will be performed. Adhesiolysis will then be performed to free the abdominal wall. Once free, a posterior rectus sheath release will be performed bilaterally. If the surgeon determines rectus sheath alone is inadequate to facilitate hernia repair than a transversus abdominis release (TAR) is performed. This is performed by dividing the transversus abdominis muscle and developing the pre-peritoneal plane to the psoas muscle bilaterally. The neurovascular perforators in the retro-rectus space are identified and preserved. Next, the posterior sheath is closed in the midline with absorbable sutures and a piece of permanent synthetic mesh is placed into the retromuscular pocket. Fixation of the mesh is at the discretion of the surgeon. The anterior rectus sheath is then closed with either a running suture or figure of eight interrupted sutures. Drains are left at the discretion of the surgeon.

**Robotic retromuscular mesh hernia repair (Intervention arm):** In brief, robotic ports are placed intra-abdominally and adhesiolysis completed. If a retro-rectus repair alone is deemed sufficient, then either a single-dock retro-rectus repairs is performed or an enhanced-view totally extra-peritoneal (eTEP) approach can be utilized based on surgeon judgement and expertise. A trans-abdominal single dock retro rectus repair begins with incision of the ipsilateral posterior rectus sheath at least 5 cm lateral to the edge of the fascial defect and developing the ipsilateral retromuscular plane to the linea alba. The preperitoneal space is then entered at the midline by incising the posterior rectus sheath posterior to the linea alba. The peritoneum is kept intact and used to cross over to the opposite side of the abdomen in the midline. The contralateral posterior rectus sheath is then incised, and dissection continued to the semilunar line on the opposite side of the patient. The midline posterior sheath and/or peritoneum is closed with absorbable suture and the anterior fascial defect is closed with a running barbed suture. A permanent synthetic mesh is then placed into the retromuscular pocket and the initial incision in the ipsilateral posterior sheath is closed to completely exclude the mesh from the abdominal cavity. If an eTEP is performed, the dissection is similar to the single dock retrorectus repair, however, the robotic ports are all placed within the retromuscular space, and only bilateral retrorectus dissections are performed without entering into the abdominal cavity. The peritoneum may be used in the midline as tissue coverage if needed.

Alternatively, if a robotic TAR is thought to be needed after assessing the hernia following adhesiolysis, then the surgeon will proceed with incision of the contralateral posterior sheath 1 cm from the linea alba and developing that retro-rectus space to the semilunar line. The transversus abdominis muscle is then divided and dissection carried laterally to the psoas muscle in the pre-peritoneal plane. Three robotic ports are then placed in the retromuscular plane, and a similar dissection is performed on the contralateral abdominal wall. The posterior rectus sheath is then reapproximated in the midline with running absorbable suture. The anterior fascia is then closed with running absorbable suture. A permanent synthetic mesh is then deployed against the closed posterior layer. Drains are left at the discretion of the surgeon. 

### Criteria for discontinuing or modifying allocated interventions

The primary endpoint will be analyzed via intention-to-treat. In the case that a patient is randomized, but the allocated procedure is not completed for technical reasons, they will be analyzed based on randomization. If patients require reoperation with conversion to the alternative treatment arm, all subsequent adverse events will be attributed to the randomized allocation.

